**Antigenic drift / emergence of new strains**

Comparisons of V/E by time period will also inform this.

**Interaction with influenza, causing more severe disease and outcomes**

Dual influenza and COVID-19 infection during the end of the 2019/20 flu season appeared to be associated with increased mortality, hence interaction of influenza and COVID-19 outcomes could be important. The number of co-infections (SARS-CoV-2+, influenza+) appearing in sentinel swab data will be monitored.

**4.7 UKHSA time / workload required**

These large analyses are slow to run. Running of analyses and extraction of results will require approx. 10 full working days.

**5. Dissemination of results**

First V/E estimates will be disseminated among the research team asap.

We would envisage papers to be written for the cohort and TND analysis.

**6. Ethical approval**

The legal basis for conducting this study is Regulation 3 of The Health Service (Control of Patient Information) Regulations 2002, and the work of the Oxford-RCGP RSC with respect to disease surveillance, vaccine effectiveness and safety is specifically approved by UKHSA’s Caldicott Guardian.

**7. Logistical aspects**

The work described here is part of an ongoing programme which will continue according to funding availability.

It is essential that this work continues to ensure data quality and for the entering of swab test results into the records.

It is our expectation that the considerable other costs associated with this project will be absorbed nationally to cover data analysis and report writing.

**8. Key deliverables**

1. Training of practices
   1. Dashboard and observatories to encourage data quality^[[10]](#footnote-10),^^[[11]](#footnote-11)^
   2. Seminar series
   3. Online information at <https://orchid.phc.ox.ac.uk>
   4. Social media
      1. Twitter
      2. Facebook
      3. Linked-in
   5. Work with RCGP and others to raise awareness of the importance of the network, clinical coding etc.
2. Ensuring electronic GP record is updated with swab and vaccine status
   1. Direct feedback to practices by practice liaison team
3. Delivery of data extracts to UKHSA
4. Publicly available data
   1. Vaccine effectiveness papers – led by UKHSA
   2. Ad hoc papers covering areas of mutual interest.

| The subsidiary studies implicit in this proposal will be undertaken in accordance with available funding |
| --- |

**Study 2: Estimation of flu vaccine effectiveness using sentinel practice schemes in the United Kingdom: 2023/24 Proposal**

**1. Background**

Because influenza viruses constantly evolve and vaccines are reformulated every year, VE estimates from previous years cannot be used to estimate VE in the subsequent years. Having annual influenza VE estimates as soon as possible after the start of a seasonal influenza epidemic or pandemic and monitoring it along its course is essential to:

- decide on recommendations for the use of the vaccine
- target complementary or alternative public health measures (e.g. antivirals) for population segments where vaccine is less effective.
- trigger further investigations on seasonal and pandemic vaccines (improve composition, use of adjuvants, need for booster doses).

The UK introduced a universal childhood influenza vaccine programme targeted for 2-16 year old children from 2013-14. In summer 2016, the US Advisory Committee on Immunisation Practice recommended the temporary suspension of use of LAIV in the USA following the CDC assessment of the lack of effectiveness of LAIV in children in the 2015-16 season, with little evidence of significant VE; the suspension was rescinded in spring 2018. Although these results are at odds with those seen in several other countries using LAIV, including the UK, it will be important to ensure the evaluation of the effectiveness of LAIV in children.

In recent seasons, it has become apparent that the current inactivated influenza vaccine programme provides sub-optimal protection to the age-groups >65 years of age, especially against influenza A/H3N2. Adjuvanted vaccines have been preferentially recommended since the 2018/19 season to all in this age-group. Since 2019/20, cell-based quadrivalent vaccines have also been available and used preferentially over standard-dose egg-based vaccines. The recombinant vaccine has also been available since 2021/22, though uptake has been low. In addition, all adults 50-64 years of age have been eligible to receive either cell or egg-based quadrivalent influenza vaccines since the 2020/21 season with the aim of reducing pressure on the health service during the COVID-19 pandemic. It is thus critically important to obtain accurate estimates of the relative effectiveness of these influenza vaccines in the relevant age groups targeted with different vaccine types (2-17, 18-64, 65+), and bringing together data from across the UK will help this aim. This proposal concerns the use of the test-negative case control method to estimate influenza vaccine effectiveness using the various UK sentinel GP swabbing schemes, with a particular focus on the absolute and relative effectiveness of these vaccines.

Further, some influenza positive sentinel swabs are targeted for genetic characterisation. Exploring vaccine effectiveness by sub-clade may help us better understand the impact of antigenic drift on vaccine effectiveness and inform vaccine strain selection. Bringing together this information from sentinel schemes across the UK helps maximise our potential to produce vaccine effectiveness estimates by sub-clade and optimize use of this valuable data.

Finally, a number of RSV vaccines are approaching licensure. There is a need to establish systems to monitor the baseline epidemiology of RSV prior to introduction of these vaccines and for this to then provide a platform to monitor the RSV vaccine programme impact and effectiveness. The burden of disease due to RSV is increasingly being recognised – particularly in young infants and also potentially the elderly, though questions remain. There is a need to establish RSV disease burden in the UK, particularly in younger children and the elderly to inform optimal future use of these new vaccines and to provide a baseline for subsequent impact studies stage.

**2. Aim and Objectives**

**2.1 Aim**

For the 2023/24 season, the aims are to:

- Estimate the pooled influenza vaccine effectiveness for laboratory confirmed infection in primary care across three age groups: children aged 2-17, working-age adults 18-64 and the elderly aged 65+ in the UK.
- Monitor RSV epidemiology in primary care with a focus on children <5 years of age

**2.2 Primary objectives**

The primary objective is to estimate 2023/24 seasonal influenza vaccine effectiveness (VE):

- Overall for any flu type,
- by influenza type (A or B),
- by influenza subtype (A/H1 or A/H3);

within each of 3 broad age groups:

- 2-17 years (and stratified by nasal vs quadrivalent inactivated vaccine),
- 18-64 years of age (and stratified by QIVc vs QIVr vs QIVe),
- >65 years of age (and stratified by aQIV and QIVc).

To describe the epidemiology of RSV in children.

**2.3 Secondary objectives**

To estimate:

- VE by risk status
- VE by influenza main clades/sub-clades
- VE by time since vaccination
- VE by period (depending on circulation patterns)
- VE by prior vaccination status in 2022/23 overall and by type/sub-type (England, Scotland)
- The interaction of age and VE in adults age 18+
- VE against asthma/COPD exacerbation (England only)

**3. Methods**

**3.1 Study designs**

- Test-negative case-control (TNCC) design will be used to estimate VE.
- For RSV descriptive statistics on swab positivity will be collated, by age group, gender, month and risk status.

**3.2 Study population and data source**

**Definitions**

The study will be undertaken in the registered population of sentinel general practice surveillance networks across the UK that undertake respiratory swabbing, details of which have been outlined previously. The surveillance schemes are: Royal College of General Practitioners (RCGP) Research and Surveillance Centre (RSC), Public Health Wales Communicable Disease Surveillance Centre Sentinel GP Surveillance, Public Health Scotland (PHS) CARI surveillance programme.

The study population will be patients presenting to their general practitioner (GP) during the 2023/24 influenza season study period with an acute respiratory illness fitting the case definition (influenza-like illness [ILI] or an acute respiratory infection [ARI]). A registered patient will be fully registered (not temporary) with a valid NHS or CHI number and no qualification period.

ILI is defined as an individual presenting in primary care with an acute respiratory illness with physician-diagnosed fever or complaint of feverishness in the previous 7 days. Acute is defined as sudden onset of symptoms.

Cases will be patients who test positive for influenza A or B virus by real-time PCR.

Controls will be patients with the same symptoms who tested negative for influenza A and B, and negative for SARS-CoV-2.

**Study Site Settings**

| English RCGP/UKHSA scheme:  Patients who contacted their GP, where the GP was part of the Royal College of General Practioners Research and Surveillance Centre (RCGP-RSC) sentinel scheme, and who had a sentinel respiratory swab taken with a result for influenza during the 2023/24 influenza season. Indications for swabbing are influenza-like illness, COVID19-like illness, an acute respiratory infection or exacerbation of asthma/COPD with onset within the last 10 days. Patients are either swabbed and consented by their GP as part of a face-to-face consultation, or directed to take a postal self-swab by GPs through takeatestuk.com after being issued a voucher code. All sentinel swabs are tested for respiratory infections including influenza and RSV using RT-PCR at UKHSA’s Virus Reference Laboratory. Vaccination data are available via linkage to GP records. |
| --- |

| Scottish PHS scheme:  Patients who contacted their GP, where the GP was one of around 140 sentinel practices taking part in the CARI surveillance programme, and who had a respiratory swab taken with a result for influenza during the 2022/2023 influenza season. Indications for swabbing were acute respiratory infection (ARI) with sudden onset within the last 7 days, and aligning with the ECDC definition of ARI. Patients are either consented and swabbed by their GP face-to-face, or they use a self-swabbing kit to take the swab themselves. All sentinel swabs are multiplex tested for 10 respiratory infections at the West of Scotland Specialist Virology Centre and results are held by ECOSS (national database of all virology test results). Vaccination data are available for adults only from the Vaccine Management Tool (VMT). All date can be record-linked using the CHI number. |
| --- |

| Welsh scheme:  Patients who contacted their GP, where the GP was part of the Public Health Wales Sentinel GP Sentinel GP Surveillance Network, and who had a sentinel respiratory swab taken with a result for influenza during the 2022/23 influenza season. Indications for swabbing are influenza-like illness, COVID19-like illness or an acute respiratory infection with onset within the last 10 days. Patients consulting in person are swabbed and consented by their GP as part of a face-to-face consultation or provided with a postal self-swab kit by GPs if consulting via telephone. All sentinel swabs are tested for respiratory infections including influenza and RSV using RT-PCR at Public Health Wales Specialist Virology Centre. Vaccination status is provided by the GP at time of consultation, either sourced from the patients’ medical records or self-reported by the patient to the GP. |
| --- |

**3.3 Study period**

The start of the influenza vaccination campaign is usually in mid-September as soon as influenza vaccine becomes available. It is theoretically available until supplies run out, although the bulk is delivered in late September through to November. The bulk of childhood vaccinations in Primary schools are delivered October to December.

The study period will commence from 4 September 2023 (the point when influenza vaccination rollout and influenza and RSV transmission may begin) and continue for the duration of the UK influenza season. An early calculation of VE will be performed prior to the February 2024 WHO strain selection committee meeting, with a full analysis carried out at the end of the season.

This proposal relates to an ongoing programme of disease surveillance. The end of the influenza season is not fixed *a priori*. The period of influenza activity is determined using data from the national influenza surveillance system.

RSV statistics will be collated at the end of the influenza season using the same season definition as for influenza.

**3.4 VE exposure**

**Definition**

Patients will be defined as vaccinated if they have received the 2022/23 seasonal vaccine at least 14 days before the date of the swab. Note that 2 doses of LAIV are recommended for some children, but will be considered vaccinated from 14 days after the first dose.

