**Previous vaccination**

Influenza vaccination in the previous season (2022/23)

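### Study 2, section 3.4 defines the primary influenza exposure by the 2022/23 vaccine, contradicting the study's own 2023/24 objective, study period and data items

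*Protocol*

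**What the plan says.** Study 2, section 3.4 (Definition) counts patients as "vaccinated if they have received the 2022/23 seasonal vaccine at least 14 days before the date of the swab". Section 3.6 adds the 14-day rule for adults and a separate recent-vaccination category, but does not say which season's vaccine is meant. Section 3.4 is therefore the only text that ties exposure to a particular vaccine.

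Section 2.2 states the target: "The primary objective is to estimate 2023/24 seasonal influenza vaccine effectiveness (VE". Section 3.2 places the study population "during the 2023/24 influenza season study period with an acute respiratory illness fitting the case definition", and section 3.3 starts the study on 4 September 2023.

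The scheme descriptions under Study Site Settings disagree with one another. England takes patients "who had a sentinel respiratory swab taken with a result for influenza during the 2023/24 influenza season". Scotland takes patients "who had a respiratory swab taken with a result for influenza during the 2022/2023 influenza season". Wales takes patients "who had a sentinel respiratory swab taken with a result for influenza during the 2022/23 influenza season".

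**The concern.** The exposure definition decides which cell of the case-control table each patient enters. Here it names a vaccine that is not the subject of the primary objective. The background to Study 2 says that VE from earlier years cannot stand in for later years because the vaccine is reformulated annually, so the literal rule also defeats the study's stated reason for existing.

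Three national schemes contribute to a pooled estimate, and their vaccination data come from different sources: GP-record linkage in England, a vaccine management system in Scotland, and GP-held or patient-reported status in Wales. A single correct definition is what holds the pooling together. As it stands, a reader cannot tell from the exposure rule alone which exposure was prespecified.

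**Working it through.** **Step 1: season labels side by side (all Study 2).**

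| Place | Season named |
| --- | --- |
| 2.2 Primary objectives | 2023/24 |
| 3.2 Population definition | 2023/24 |
| 3.2 English scheme | 2023/24 |
| 3.2 Scottish scheme | 2022/2023 |
| 3.2 Welsh scheme | 2022/23 |
| 3.3 Study period | from 4 September 2023 |
| 3.4 Exposure definition | 2022/23 vaccine |
| 3.8 Table 1, current vaccination (status, date, route, type) | 23_24 |
| 2.3, 3.7 and 3.8 Table 1, prior vaccination | 2022/23 |

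The exposure rule disagrees with the objective, population, period and data items. It coincides with the variable that the protocol labels as prior vaccination. No passage says that this is intended.

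**Step 2: what the literal rule does.**

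- A patient given only the 2023/24 vaccine is unvaccinated; a patient given only the 2022/23 vaccine is vaccinated.
- Section 3.3 puts most delivery in late September to November, and primary-school vaccination in October to December. On that pattern a 2022/23 dose given as late as 31 December 2022 is 247 days old on 4 September 2023. The 14-day condition is then met automatically, and the 1-13 day category (3.6), with the date imputation that feeds it (3.10), has essentially nobody in it.
- The secondary objective of VE by 2022/23 vaccination status (2.3) fails, because exposure is constant within each stratum.
- A swab from the 2022/23 season cannot fall in a period starting on 4 September 2023. Read literally, Scotland and Wales would contribute no eligible swabs.

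**Step 3: illustrative size.** Study 2 states no coverage, power or expected VE, so there is no figure of its own to reproduce. All inputs here are assumptions:

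- c, 2023/24 coverage in controls: 0.30 to 0.70
- a, probability of a 2022/23 dose given a 2023/24 dose: 0.70 to 0.95
- b, probability of no 2022/23 dose given no 2023/24 dose: 0.80 to 0.95
- no residual effect of the 2022/23 dose; true odds ratio θ = 1 − VE

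With the 2022/23 flag used as exposure:

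- control odds = [ca + (1−c)(1−b)] / [c(1−a) + (1−c)b]
- case odds = [cθa + (1−c)(1−b)] / [cθ(1−a) + (1−c)b]
- apparent VE = 1 − case odds / control odds

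For a true VE of 50% (θ = 0.5):

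| c, a, b | Control odds | Case odds | OR | Apparent VE |
| --- | --- | --- | --- | --- |
| 0.30, 0.70, 0.80 | 0.350/0.650 | 0.245/0.605 | 0.752 | 24.8% |
| 0.40, 0.85, 0.90 | 0.400/0.600 | 0.230/0.570 | 0.605 | 39.5% |
| 0.70, 0.95, 0.95 | 0.680/0.320 | 0.3475/0.3025 | 0.541 | 45.9% |

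The first and last rows are the extremes of the combinations tried. For a true VE of 30% the same two corners give 14.4% and 26.9%.

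**The case against.** The strongest reply is that this is a stale label in an otherwise consistent 2023/24 design. The population definition and study period are right. Table 1 requests status, date, route and type for 2023/24, but only a status field for 2022/23, so the primary stratification by vaccine type could not be run on a 2022/23 exposure. The prior-vaccination objective is limited to England and Scotland. The 1-13 day category, the exclusion of children vaccinated 0-20 days before onset, and the imputation of dates from patients swabbed in the same week make sense only for a current-season dose. The wording looks carried over from the previous year's proposal.

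Most of this stands, and it rules out three stronger readings that a reader might infer.

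- That the study as a whole estimates the wrong season's effect. This follows only if section 3.4 is applied literally, and much of the other operative text points the other way.
- That the pooled VE mixes two exposures. This would require a scheme to depart from the 23_24 fields in Table 1, and nothing suggests that one would.
- That the Scottish and Welsh populations are defined as 2022/23. Those labels sit in site descriptions, while the general population definition and study period say 2023/24. This is an internal contradiction, not a uniformly wrong rule.

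What the reply does not do is make section 3.4 correct. It shows what was probably meant; it does not supply another definition of exposure.

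**Conclusion.** The point holds as an error in an operative rule. The sole definition of the primary exposure names the wrong season's vaccine, and it should be corrected before analysis. The Scottish and Welsh labels are lesser contradictions of the same kind.

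The attenuation from a true 50% to about 25-46% is conditional on the 2022/23 flag actually being used, and on assumed coverage, assumed concordance and no residual protection from the earlier dose. It is neither a forecast nor a bound. The Table 1 fields make use of the correct season the more likely outcome.

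**What to change.** - In section 3.4, define vaccinated as having received the 2023/24 seasonal vaccine at least 14 days before the date of the swab.
- In the Scottish and Welsh scheme descriptions, change the season to 2023/24, in line with sections 3.2 and 3.3.
- Keep 2022/23 only for the prior-vaccination variable (2.3, 3.7 and Table 1).
- While doing so, check whether the reference in section 3.8 to strains circulating in 2022/23 is intended.

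The cost is three wording corrections and a notice to the contributing schemes. Table 1 already requests the right fields, so no new data are needed and no sample-size figure changes.

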**Ascertainment**

Vaccination history is based on electronic health records, which may be supplemented by vaccination information given on the swabbing form if available. Vaccination dates are required, ideally accompanied by vaccine type (LAIV-intranasal; injectable-QIVe, injectable-cell-based QIVc, injectable-egg-based QIVe injectable recombinant QIVr and adjuvanted injectable-aQIV).

**3.5 VE outcome(s)**

The PHS definition of ARI (sudden onset within last 7 days) is –

• Sudden onset of symptoms

• At least one of the following four respiratory symptoms:

o Cough

o Sore throat

o Shortness of breath

o Coryza

AND

• A clinician's judgement that the illness is due to an infection.

The RCGP and Welsh scheme suggest swabbing with onset within the last 10 days, this was extended during the COVID-19 pandemic. However, influenza positivity is highest within the first 7 days, so analyses will aim to restrict to the 0-7 day post onset window.

For the 2023/24 season RCGP are broadening their definition for swabbing to include asthma and COPD exacerbations. These swabs will be excluded from main analyses (where known), and explored in secondary analyses if there are sufficient swab numbers.

Cases are defined as patients with a positive test for influenza, while those with a negative test for influenza and SARS-CoV-2 (but who could have tested positive for other pathogens) are classified as controls.

**3.6 VE exclusion criteria**

Registered patients may be excluded if they have expressed a wish to be excluded from the surveillance programme; or opted out of sharing their data. However, those who consent to a virology swab will include in their consent record sharing for this purpose.

We ideally look for swabs to fall within 0-7 days of reported illness onset. However, patients will not be excluded where no onset date is given or if the number of days between onset and swab exceeds 7 days (the impact of missing and longer onsets will be explored and multiple imputation methods used). Swabs with implausible onset dates post sample receipt will be retained and the onset date replaced as missing.

Patients must have both a negative influenza A and an influenza B result present to be included as a control.

Patients with nonsensical vaccination histories (e.g. outside the flu season, adults that received LAIV, children that received aQIV) or swab dates (e.g. if swabbed after date of receipt) will be excluded, as will swabs received >21days after the reported date taken.

The study will include only those with known age between 2 and 105 and known sex.

Patients residing outside the boundaries of their respective schemes will be excluded i.e. RCGP/UKHSA patients must be resident in England, PHS patients must be resident in Scotland.

Patients with unknown vaccination status will be excluded. This will include patients with no linkage to either NIMS or a GP record in England, and patients for whom no definite yes/no response to the question on vaccination status was recorded on the Welsh swabbing form. Scottish patients will be assumed to be unvaccinated if no record of vaccination is found.

LAIV-eligible patients aged 2-17 will be excluded if they were vaccinated 0-20 days before symptom onset, or if no vaccination date is available, to ensure positives are not related to LAIV. Patients aged 18+ will not be considered fully vaccinated until 14-days post vaccination. Those swabbed during days 1-13 post vaccination will be included in analyses and assigned a separate exposure category for recent vaccination. Vaccinated adults aged 18+ will not be excluded if no vaccination date is available, instead a multiple imputation approach will be used.

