**Flu TNCC**

For analysis of this test-negative case-control study, logistic regression will be used to calculate the unadjusted odds ratios for influenza vaccination in cases compared to controls, with a 95% confidence interval. This will be used to calculate an unadjusted VE as unadjusted VE=1-OR.

Logistic regression will be used to calculate the odds ratio for vaccination, adjusted for week of swab, scheme and age group, and additionally for relevant characteristics which change the vaccine effect by ≥1% (including risk status and sex). This will be used to calculate the adjusted VE. This will be undertaken for all cases/controls in the elderly, working-age adults and children separately, and in relevant subgroup analyses.

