**Missing data**

We will aim to use multiple imputation methods for our main analysis where possible, rather than exclude data. However, data on vaccination status, age group and date of swab must be complete for inclusion in the study.

*Multiple imputation for missing risk status*

Multiple imputation methods will be used for missing data on risk status, taking into account patient age, and vaccination history and age eligibility.

*Multiple imputation for missing onset date*

Multiple imputation will be used where onset dates are missing. An interaction term between vaccination status and indicator for swab within 0-7days of onset will fitted (the sample size needs to remain consistent). Where onset is missing this indicator will be imputed based on the proportion of samples with known onset falling within the 7day window, taking into account positivity for flu or other viruses and patient age.

*Multiple imputation for missing vaccination date*

Where an adult patient has indicated that they were vaccinated at the time of the swab, but no vaccination date was given, a hot-deck imputation approach will be used. Vaccination dates will be sampled from other vaccinated patients within the same broad age cohort (18-64 or 65+) and swabbed within the same week. The imputed vaccination dates will be used to assign patients as within 1-13 days of vaccination or fully vaccinated.

In secondary analyses by vaccine type, a category for unknown vaccine type will be included. (Since vaccine type is almost universally missing for patients whose vaccination date is missing, the above imputation approach for vaccination dates need not be taken for analyses of vaccine type).

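### Influenza study: the no-record-means-unvaccinated rule for Scotland has no age limit, although the named Scottish source covers adults only, so vaccinated Scottish children would be analysed as unvaccinated

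*Protocol*

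**What the plan says.** All references are to Study 2, the influenza study.

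- **Source of Scottish vaccination data** (3.2, Study Site Settings, Scottish scheme): "Vaccination data are available for adults only from the Vaccine Management Tool (VMT"). No source is named for Scottish children.
- **Rule for a missing Scottish record** (3.6): "Scottish patients will be assumed to be unvaccinated if no record of vaccination is found". No age limit is given.
- **General rule** (3.6, same paragraph): "Patients with unknown vaccination status will be excluded". It is spelled out for England and Wales before the Scottish sentence departs from it. The Missing data part of 3.10 adds that "data on vaccination status, age group and date of swab must be complete for inclusion in the study".
- **Who is in the analysis**: the 2.1 aim is a pooled estimate for "children aged 2-17, working-age adults 18-64 and the elderly aged 65+ in the UK". Section 3.2 lists the "Public Health Scotland (PHS) CARI surveillance programme" among the contributing schemes. The only age restriction in 3.6 is "The study will include only those with known age between 2 and 105 and known sex".
- **Model** (3.10, Flu TNCC): an unadjusted VE, then a logistic model "adjusted for week of swab, scheme and age group".

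**The concern.** For adults the Scottish rule is reasonable: a vaccination register exists, so absence from it is informative. For children the named source holds nothing, and absence from it says nothing about vaccination. The rule therefore turns an unknown exposure into a definite and often wrong one.

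VE in 2-17-year-olds, split by nasal and inactivated vaccine, is a primary objective (2.2). At stake are the unadjusted child VE, the description of cases and non-cases by vaccination status, and possibly the adjusted VE. There is a further effect. Section 3.6 excludes LAIV-eligible children vaccinated 0-20 days before onset so that positives are not due to the live vaccine. That exclusion cannot be applied to a child with no vaccination record, so a recently vaccinated Scottish child could enter as an unvaccinated case.

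**Working it through.** **1. Following the text for one child.** Take a vaccinated Scottish 8-year-old who is swabbed. The scheme is in the study, the age is within range, and the named register does not cover the child. The Scottish sentence in 3.6 then assigns the status unvaccinated. No other sentence clearly removes the child.

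**2. Unadjusted VE.** The protocol gives no figure to reproduce. All inputs here are assumptions: true OR 0.5 (VE 50%), 45% of child swabs from vaccinated children, 25% positivity in the unvaccinated, the same in every scheme, and a Scottish share *s* of child swabs.

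- Odds of a positive swab: unvaccinated 0.25/0.75 = 1/3; vaccinated 0.5 × 1/3 = 1/6, so positivity 1/7.
- Per swab, coded correctly: vaccinated positive 0.45/7 = 0.0643, vaccinated negative 0.3857, unvaccinated positive 0.1375, unvaccinated negative 0.4125. OR = (1/6)/(1/3) = 0.5.
- Per Scottish swab, all coded unvaccinated: positive 0.1375 + 0.0643 = 0.2018; negative 0.4125 + 0.3857 = 0.7982.
- Pooled OR = (1/6) × U0/U1, with U1 = (1−s) × 0.1375 + s × 0.2018 and U0 = (1−s) × 0.4125 + s × 0.7982.

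| s | U1 | U0 | OR | Unadjusted VE |
|---|---|---|---|---|
| 0.15 | 0.1471 | 0.4704 | 0.533 | 46.7% |
| 0.33 | 0.1587 | 0.5398 | 0.567 | 43.3% |
| 0.50 | 0.1696 | 0.6054 | 0.595 | 40.5% |

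The direction is not fixed. A second set of expected counts used 30-50% coverage in controls and Scottish shares of 10-50%. If the case:control odds in the unvaccinated are 0.40 in Scotland against 0.25 elsewhere, unadjusted VE is too high: 61-66% for a true 60%, and 43-52% for a true 40%. With equal control coverage and correct coding the crude OR would equal the true OR, so this shift also comes from the miscoding.

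**3. Adjusted VE, scheme only.** In the same expected counts with scheme in the model, adjusted VE stays at the true 60% or 40%. A Scottish stratum with no vaccinated children carries no information on vaccination.

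**4. Adjusted VE, week and scheme.** The protocol also adjusts for week. Week terms are shared across schemes, so miscoded children help to estimate them. As uptake rises, positivity among Scottish children labelled unvaccinated drifts down, and this leaks into the week terms. The fits below use expected counts over 20 weeks, true VE 50% and uptake rising to 50%, at Scottish shares of 15/33/50%:

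| Scottish epidemic timing | Adjusted VE |
|---|---|
| Same as elsewhere | 49.7 / 49.4 / 49.1% |
| Peak one week earlier | 49.0 / 47.7 / 46.5% |
| Peak two weeks earlier | 47.8 / 45.2 / 42.7% |
| Peak one to three weeks later | 50.2 to 51.5% |

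Correct coding gives 49.6-49.9% in the same models, so nearly all of the error is due to the miscoding. With the same timing and uptake spread over 6, 10 or 15 weeks, the shortfall is 0.2-0.4 points at a 15% share, 0.4-0.9 at 33% and 0.6-1.3 at 50%. With constant coverage it is practically nil. Across wider uptake settings, a two-week shift in Scottish timing gives errors from about 8 points too low to about 4 points too high.

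**5. Partial rescue by forms.** If forms identify 30% of vaccinated Scottish children, the Scottish stratum does inform VE, and wrongly. Scheme-adjusted VE becomes 57-60% for a true 60% and 37-40% for a true 40%.

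**The case against.** **The text may not instruct miscoding.** The Scottish sentence can be read as applying only where a source was searched. Where no source covers the age group, the general exclusion of unknown status would govern, and the data specification in 3.8 does have a code for unknown vaccination status. That is a sensible intention, but the sentence refers to Scottish patients without limit and stands as an exception to the general rule. An analyst following it would code children as unvaccinated.

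**Other sources.** Section 3.4 lets swab-form information supplement records. A reader might infer that every vaccinated Scottish child is miscoded. That is slightly too strong, because this route is open to any scheme. However, no Scottish form question is described, whereas the Welsh one is, and step 5 shows that partial capture does not solve the problem. The sentence on the Scottish source could also mean that adult data come only from the VMT, but then there is still no child source.

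**The LAIV clause.** Section 3.6 also excludes LAIV-eligible children with no vaccination date. This must mean vaccinated children without a date, or it would remove every unvaccinated child.

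**The adjusted VE is protected.** This largely stands. A reader might infer a fixed downward bias of 1-2 points in the adjusted estimate. The documents do not support that: size and sign depend on Scottish share, timing and uptake, none of which they give. Nor does such a figure breach a tolerance set by the protocol, since the 1% change in 3.10 is a rule for selecting covariates.

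**The publication rule.** A reader might also infer that the minimum expected cell count of 10 is compromised. This is not shown. At 45% coverage and 25% positivity the smallest expected cell is vaccinated cases, which is the number vaccinated times overall positivity. Added children labelled unvaccinated leave the number vaccinated unchanged, so this cell moves only if Scottish positivity differs.

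**Conclusion.** The concern holds. Taken literally, the Scottish rule misclassifies exposure in an age group that belongs to the primary objective, and it contradicts the protocol's own treatment of unknown vaccination status.

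The unadjusted child VE and the vaccination-status table would be wrong, by roughly 3 to 9 points in the unadjusted VE under the inputs of step 2 and with a direction that depends on Scottish positivity. The LAIV safeguard cannot work for these children. The adjusted VE is mostly protected by the scheme term. Its error is mostly below 1 point with common epidemic timing, and can be several points in either direction if Scottish timing differs while uptake is rising. Every size here rests on assumed coverage, VE, positivity, Scottish share and timing. The conflict in the text does not depend on them.

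**What to change.** In 3.6, limit the no-record-means-unvaccinated rule to Scottish patients aged 18 and over. State that Scottish patients aged 2-17 have unknown vaccination status and are excluded from all influenza VE analyses and vaccination-status tables, unless a Scottish source of child vaccination data is named and linked. If they are excluded, label the child estimate as England and Wales, and qualify the UK scope in 2.1 for that age group. If a source is linked, the UK scope can stay.

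The cost is one sentence and one filter, fewer child swabs, and a narrower geographic scope for the child estimate. Where there is no vaccination record, the swabs lost carry no usable information on vaccination. The RSV description does not need vaccination status and can keep these children, apart from its breakdown by vaccination status.
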